### Data monitoring

A clinical trial monitor, appointed by the sponsor, periodically supervises the study progress in each participating site to ensure patient rights and well-being are safeguarded, that the protocol, ethical requirements, Good Clinical Practice (GCP) standards and applicable regulations are being followed, that the necessary documentation is available and that collected data reflect exactly data recorded on the CRF. External auditors are regularly appointed by the sponsor for independent supervision of trial activities and conduct.

An independent Data Safety Monitoring Committee (DSMC) has been created as an advisory board to guarantee correct patient enrolment and withdrawal, to counsel on safety matters in interim analyses as well as throughout the duration of the trial, to provide advice on statistical issues and to be involved in any decision ensuring the compliance of GCP, protocol procedures and applicable regulations. This committee includes 4 members, independent from sponsor or clinical teams, including 2 clinical advisers in the field of cardiology, 1 clinical methodologist, and 1 expert in ethical issues.

### Safety and adverse events assessments

In accordance with GCP guidelines, all AEs and SAEs that may occur during the clinical trial (observed by the investigator or reported by the patients) whether or not attributed to the investigational medicinal product, are closely monitored until resolution or stabilization, and registered in the study CRF. Also, investigators report to the sponsor all SAEs within the first 24 h from awareness of the event. AEs will be classified on the basis of the Medical Dictionary for Regulatory Activities (or MedDRA) terminology and summarised for each treatment group and relationship to the intervention. Causality of AEs with the study intervention is assessed by the investigator, and re-evaluated by a person responsible for pharmacovigilance appointed by the sponsor. Furthermore, trial DSMC may review accumulated safety data, when appropriate, and for advising the sponsor concerning the continuation, amendment and termination of the trial.

The clinical trial will be interrupted, if any of the following conditions arise: acute arrhythmia in 3 or more patients randomised to the experimental group, severe toxicity as per WHO scale (> grade 3) related to the infusion of BMMNCs in 3 or more patients, major infections caused by the extraction or infusion procedures in 3 or more patients or mortality related to the infusion of the cell product in 2 or more patients. Trial can also be prematurely ended if the sponsor finds a reasonable cause such as: publication in the scientific literature of unacceptable risks or AEs for patients; or a similar study showing consistent results of no significant health benefits; insufficient commitment by the coordinating or principal investigators; or substantial modifications or suspension of the development of the drug under investigation.

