### Randomisation and blinding process

Randomisation is centrally performed by the sponsor, stratified by age (> or ≤ 45 years old) in a 2:1 block randomisation allocation BMMNCs or placebo. As sample size is small and both planned interim analysis may require a balanced distribution of the subjects within both study groups, block randomization is applied. Randomization list was computer generated by the Sponsor, and allocation is kept concealed for the research teams recruiting patients.

Investigators and patients (as well as clinical monitors) are blind to the treatment assigned. In the case of SAE, when the patients’ management could be improved by the knowledge of the blinded treatment assigned, the principal investigator may request the sponsor formal permission for subject unblinding. Additionally, specific unblinding of patients allocated to the control group may be authorized by the sponsor to allow for the treatment through compassionate use with their own previously cryopreserved BMMNCs.

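### The automatic interruption conditions for death and for severe toxicity count only infusion-related events, so the same harm from the marrow harvest or the month-6 catheterisation triggers neither

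*Protocol article*

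**What the plan says.** Protocol article, Safety and adverse events assessments, makes interruption compulsory if any one of four conditions arises:

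- Arrhythmia: "acute arrhythmia in 3 or more patients randomised to the experimental group". The arm is restricted, the cause is not.
- Toxicity: "severe toxicity as per WHO scale (> grade 3) related to the infusion of BMMNCs in 3 or more patients".
- Infection: "major infections caused by the extraction or infusion procedures in 3 or more patients".
- Death: "mortality related to the infusion of the cell product in 2 or more patients".

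The same section adds two discretionary routes. One is that the "trial DSMC may review accumulated safety data, when appropriate" and advise the sponsor on continuing, amending or ending the trial. The other is "Trial can also be prematurely ended if the sponsor finds a reasonable cause", followed by a list of examples that is not closed.

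Two invasive procedures other than the infusion matter here. Manufacturing of BMMNCs/placebo states that all patients, placebo patients included, have 100–180 mL of marrow drawn in 20–30 aspirations. Study outcomes schedules cardiac catheterisation on the infusion day and again at month 6.

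**The concern.** The conditions differ in which causes they accept. The infection condition accepts the harvest. The death and toxicity conditions, which deal with the gravest outcomes, accept only the infusion. Yet the trial also exposes patients to the harvest and to a later catheterisation. The Discussion recognises the latter as hazardous: it limits ventricular angiography to two assessments to reduce risk, and it mentions contrast-induced kidney injury.

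As written, two deaths from the infusion oblige the trial to pause, while two deaths from the harvest or the month-6 catheterisation do not. The same holds for three patients with toxicity above grade 3. Whether the trial pauses would then rest on judgement and not on the stated rule.

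**Working it through.** **Coverage of the four conditions, read literally**

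| Condition | Count | Harvest harm counted? | Month-6 catheterisation harm counted? |
|---|---|---|---|
| Acute arrhythmia | 3 | Yes, experimental arm only | Yes, experimental arm only |
| Toxicity above grade 3 | 3 | No | No |
| Major infection | 3 | Yes | Not named |
| Death | 2 | No | No |

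Fatal bleeding after the harvest, or severe kidney injury after the month-6 angiogram, would therefore meet none of the four. The infusion-day catheterisation can be read as part of the infusion and is left out of the point.

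**Patients exposed.** Sample size calculation gives 17 + 34 = 51. This reproduces:

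- The SD of the change is 10 × √(2 × (1 − 0.5)) = 10.
- With a difference of 9, two-sided alpha 0.05, power 0.8 and 2:1 allocation, the placebo arm needs 1.5 × (1.96 + 0.84)² × 10² / 9² ≈ 14.5, so 15.
- Allowing for 10% loss, 15 / 0.9 = 16.7, so 17, and 2 × 17 = 34.

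The article gives no operating figure for the interruption conditions, so there is none to reproduce. Planned procedures outside the death and toxicity conditions number at most 51 harvests + 51 month-6 catheterisations = 102. Loss to follow-up would lower the second term. These are counts of procedures, not measures of risk.

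**How likely is the uncounted harm?** The article gives no procedural harm rates, so the per-patient risk p below is an assumption. It is the combined risk from the harvest and the month-6 catheterisation, taken as independent between patients.

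For deaths, P(X ≥ 2) = 1 − (1 − p)^51 − 51p(1 − p)^50:

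- p = 0.1%: 1 − 0.9503 − 0.0485 = 0.0012 (0.1%)
- p = 0.5%: 1 − 0.7744 − 0.1985 = 0.0271 (2.7%)
- p = 1%: 1 − 0.5990 − 0.3086 = 0.0925 (9.2% from the unrounded value)

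For toxicity above grade 3, P(X ≥ 3) subtracts a further 1275p²(1 − p)^49, where 1275 = 51 × 50 / 2:

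- p = 0.1%: below 0.1%
- p = 0.5%: 0.2%
- p = 1%: 0.0925 − 0.0779 = 0.0146 (1.5%)
- p = 2%: 8.2%
- p = 5%: 47.3%

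Under the present wording, these events trigger the two conditions with probability zero, whatever p is. The figures are thus both the chance that the gap matters and the chance that the wider wording alone would cause a pause.

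**The case against.** The strongest reply is that oversight already reaches this harm. Adverse events are followed whether or not they are attributed to the product, and serious ones go to the sponsor within 24 hours. Data monitoring gives an independent DSMC, with two cardiology advisers, a safety remit throughout the trial. The sponsor's power to end the trial for a reasonable cause is open-ended. Two other compulsory conditions catch part of the harm. Tying automatic triggers to the investigational product and leaving procedural complications to expert judgement is a defensible design. All of this stands, and it limits the point to the automatic triggers. It does not close the gap: the drafters chose a compulsory rule for infusion deaths although these discretionary routes also existed.

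A reader might infer more than the documents support:

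- **That blinding makes the attribution unworkable.** The article says "Causality of AEs with the study intervention is assessed by the investigator" and "Investigators and patients (as well as clinical monitors) are blind to the treatment assigned". But the first sentence goes on to provide for re-evaluation by a pharmacovigilance person whom the sponsor appoints, and the sponsor, which holds the randomisation list, is not among those named as blind. Events can be sorted by arm at sponsor level.
- **That placebo-infusion harm is also excluded.** The wording is not settled. The BMMNCs infusion section separates placebo from cell product, while Angiographic measurement of ventricular function uses cell infusion for the whole trial.
- **That the infection condition proves a drafting error.** Marrow aspiration is a natural infection route, so naming it there is coherent in itself. The difference in scope is unexplained, but it does not show intent.
- **That two such deaths are likely.** Large probabilities need procedural death risks of several per cent. Nothing in the article suggests these.

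**Conclusion.** The point holds in a narrow form. On the stated wording, death or toxicity above grade 3 caused by the harvest or the month-6 catheterisation cannot trigger either of the two conditions written for those outcomes. This follows from the text and needs no assumption.

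Its practical weight is low. Over assumed procedural death risks of 0.1% to 1%, the chance that two or more such deaths occur among 51 patients is 0.1% to 9.2%, and the low end is the more plausible. The death condition is the firm part. Whether three is the right count for procedure-related toxicity is open, because the trigger probability rises steeply if such toxicity is not rare. The documents do not support saying that the trial lacks safety oversight or could not be stopped for procedural harm. Severity: low, an optional improvement.

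**What to change.** In Safety and adverse events assessments, replace the death condition with wording such as: *death attributed to any study product or study procedure (harvest, catheterisation or infusion) in two or more patients, in either arm*. Extend the toxicity condition to study procedures in the same way, and ask the DSMC to confirm that three remains a suitable count once procedural events are included.

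The cost is one amendment to two clauses, with no new visit, test or committee. The protocol had already been amended seven times, and recruitment was still active when the article was submitted. The downside is the chance of extra pauses shown in the working, which for deaths stays below 10% over the assumed range. If the pause leads to review by the existing DSMC, a trigger need not end the trial.

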### Ethics and dissemination

The study protocol has been approved by the Andalusian Coordinating Ethics Committee for Biomedical Research (*Comité Coordinador de Ética en Investigación Biomédica de Andalucia, CCEIBA*) and authorized by the AEMPS. All substantial amendments to the original protocol or related documents also obtained further approval from the AEMPS and the corresponding Ethics Committee (CCEIBA and *Comité de Provincial de Sevilla*). The trial protocol has been subject to seven amendments so far, including minor changes in patient eligibility criteria, participating sites and follow-up evaluations. The present manuscript describes the current approved protocol at the time of submission: Amendment 7, 16th March 2018. Neither the researchers nor the sponsor can perform any modifications to the protocol without the authorization of both the Ethics Committee and the AEMPS.

The study is being performed in accordance with the protocols and the sponsor’s standard operating procedures (SOPs). Sponsor and investigators ensure that this trial follows the recommendations of the Declaration of Helsinki (World Medical Association 2013), the International Conference Harmonization Guidelines (ICH) for GCP (CPMP / ICH / 135/95) and the current Spanish legislation in the field of Clinical Trials.

In order to guarantee the patients’ confidentiality, data generated during the study is treated in accordance with the 3/2018 Organic Law on the Protection of Personal Data and Securing of Digital Rights, Regulation (EU) 2016/679 on the protection of personal data, as well as other regulations implementing it. All personal data is kept at the hospital, and only the investigator, the trial monitor, trial auditors/inspectors, and the Ethics Committee have access.

The drug under research is considered a cell therapy medicinal product (or placebo) as defined in Directive 2001/83/EC1 as amended by Commission Directive 2009/120/EC. The sponsor of the clinical trial is holder of an insurance policy to cover for any patient who may suffer harm from trial participation. All remaining biological samples will be destroyed after the study has ended and its results have been published. Likewise, all cryopreserved tissue samples will be discarded after all patients allocated to placebo have had the right to opt for treatment (when applicable).

The sponsor and investigators are responsible for the publication of the trial results in accordance with applicable regulations to clinical trials. All items from the WHO Trial Registration Data Set were registered in the publicly accessible databases ClinicalTrials.gov (NCT02033278, January 10, 2014) and the EU Clinical Trial Register (EudraCT number: 2013–002015-98). Dissemination of results will be mainly focussed on publications in peer-reviewed scientific journals as well as presentations at national and international scientific meetings. The SPIRIT statement [41] has been observed in the publication of this study protocol and the CONSORT [42] guidelines will be guaranteed when publishing the study results in clinical journals and conferences. Trial results will also be disseminated to the public through a lay summary of results uploaded onto EU database, as well as patient congresses whenever possible.

## Discussion

DC is a heart muscle condition affecting up to 1 in 250 individuals, the majority of which are idiopathic [43]. The disease is associated with adverse outcomes, including a 20% 5-year mortality related with heart failure. Recent studies have shown that intracoronary infusion of autologous BMMNCs has a positive impact in the cardiac function of affected patients [22–29, 32, 41], but until now there are not reported studies assessing the safety and efficacy of high dose BMMNCs (5–10 × 10^8^ cells), for a follow-up period longer than one year. Other published trials evaluating the use of BMMNCs in idiopathic DC have a limited sample size, are not controlled or blinded. The present study has been designed as a randomized double-blinded and placebo-controlled clinical trial for comparing the functional recovery of patients receiving the conventional treatment for DC plus an intracoronary infusion of BMMNCs or placebo. Therefore, individuals allocated to the placebo group, as well as those receiving BMMNCs, are receiving the best standard pharmacological treatment available and are not subject to any additional risk of serious or irreversible harm, while it is possible to evaluate the true added benefit (or risk) of the BMMNCs therapy.

Patient recruitment in this trial has been proven difficult so far, due to a very low prevalence of the disease, approximately 1:250, as estimated by Hershberger et al. [43], as well as the specific clinical profile that demands the trial’s protocol. Also, this is a publicly-funded clinical trial promoted by academic clinical researchers and public health entities, which hinders the possibility to manage a larger trial with more recruiting sites. Therefore, study has been designed as a small size trial with enough power to detect a change in LVEF equal to or greater than 9%, which is considered a clinically significant difference in terms of symptomatology. However, an interim analysis is planned to allow for an adaptive sample size re-calculation based on the data from the 6 months’ post-infusion period of the first 20 patients included.

LVEF improvement is the main study variable, and it will be evaluated angiographically by an expert angiographer blinded to treatment allocation and patient’s progression. Although this technique is not the gold standard for LVEF estimation, the approach will reduce inter-observer variability and provide more accurate, repeatable results, avoiding some of the limitations of echocardiographic estimates. Cardiovascular Magnetic Resonance (CMR) was not a feasible option in the context of this study due to the high frequency of devices (Cardiac Resynchronization Therapy Defibrillator or CRT-D) in this population that interfere with CMR scans results. Also, not all participating sites had equivalent CMR techniques, which may have provided LVEF estimates based on non-comparable images, leading to increased variability of results. Consequently, the main limitation of the present trial design is its comparability across studies that measure LVEF using magnetic resonance imaging.

In order to reduce the risks of left ventricular angiography, only two assessment points are stablished throughout follow-up (at baseline and 6 months after treatment). Also, the risk of contrast-induced acute kidney injury is minimized by the exclusion of patients with serum creatinine higher than 2,5 mg/dL. However, as the moment of highest benefit (if any) after cell infusion is still unclear, complementary non-invasive measurements of LVEF using 2D echocardiography are set out at baseline, as well as at months 3, 6, 12, 18 and 24 after treatment. Although both estimates will not be interchangeable, a correlation may be stablished that will allow for drawing conclusions about the long and short-term effects of BMMNC.

In conclusion, the results of the present trial are expected to envision a new therapeutic alternative for the treatment of idiopathic DC. Current pharmacological treatments aim to improve blood flow and prevent further damage to the heart, but they are not curative. Stem cell therapy constitutes a promising alternative to palliative care, restoring cardiac structure and function. Once the safety and efficacy of this advanced therapy product is established in humans, the final goal will be to confirm these observations in future phase II and/or phase III clinical trials involving a larger number of subjects.

## Data Availability

Data availability is not applicable to this article as no datasets were yet generated or analysed.

## Abbreviations

AEMPS: Agencia Española de Medicamentos y Productos Sanitarios
AEs: Adverse events
AIAT: Andalusian initiative for advanced therapies
AMI: Acute myocardial infarction
BM: Bone marrow
BMMNC: Bone marrow-derived MonoNuclear cells
BNP: Brain natriuretic peptide
CCEIBA: Comité Coordinador de Ética en Investigación Biomédica de Andalucia
CMR: Cardiovascular magnetic resonance
CRF: Case report form
CRT-D: Cardiac resynchronization therapy defibrillator
DCs: Dilated myoCardiopathies
DSMC: Data safety monitoring committee
EDC: Electronic data capture
GCP: Good clinical practice
G-CSF: Colony-stimulating factor
HDL: High-density lipoprotein
ICH: International conference harmonization
LVEF: Left ventricular ejection fraction
MACEs: Major cardiac events
MedDRA: Medical dictionary for regulatory activities
NT-proBNP: N-terminal fragment of pro-brain natriuretic peptide
NYHA: New York heart association
SAEs: Serious adverse events
SOPs: Standard operating procedures
